**Outcomes**
*Primary Outcome*. The primary outcome measure of this study is the PAS-induced LTP-like plasticity in the S1. PAS-induced LTP-like plasticity will be assessed using CEA. CEA is quantified as the area under the curve of rectified TMS-EEG response within a time window of 25–275 ms from TMS stimulus onset [44]. This chosen time window is designed to exclude any early artifacts and account for the subsiding effects of TMS. CEA will be averaged across 100 epochs from the electrodes of interest corresponding to the S1 region. The mean post-PAS CEA will be then divided by the pre-PAS CEA, reflecting the potentiation of CEA at each of post-PAS time points (0, 15, 30, and 60 minutes). Given that the timing of the post-PAS maximum potentiation could differ among participants, we will use the maximum CEA ratio for each participant for the statistical analysis [21].

To asses TR, the total score on the “touch” category of SPQ questionnaire will be used.

**A *Priori* power calculation** A sample size of *N* = 64 participants, consisting of 32 autistic participants and 32 neurotypical controls, has been determined as adequate for hypothesis testing. This sample size provides 90% power. This calculation is based on the preliminary data, the observed LTP-like plasticity difference of 20.6 points [15], as evidenced in our PAS-EEG pilot study involving both autistic adults and control subjects. Moreover, the same sample size is deemed suitable for evaluating hypotheses 2, offering an 80% statistical power to detect a moderate effect size (Cohen’s f2 = 0.15). These power calculations were executed using G*Power [45].

Drawing upon our previously published findings [15], we envision a "substantial" impact of active rTMS in a group of 16 autistic participants when compared to a sham group also consisting of 16 autistic participants. It is important to note that, given the relatively small sample size, the application of a single session, and the exploratory nature of this outcome, our approach to presenting results and their interpretation will extend beyond statistical significance values. Instead, we will place significant emphasis on estimated effects and their precision, including the calculation of 95% confidence intervals. This comprehensive set of information, combined with data related to tolerability, will play a pivotal role in shaping the design of future clinical trials.

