## Objectives

In this study, there are four objectives:

(**1**) To assess and compare plasticity in the S1 between autistic adults and neurotypical controls.(**2**) To examine the relationship between TR and plasticity in the S1 within both study groups, i.e. autistic and neurotypical.(**3**) To investigate if a single-session of active bilateral rTMS delivered to the S1 can reduce the S1 hyper-plasticity in autistic adults.(**4**) To assess tolerability of bilateral rTMS to the S1.

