## Hypotheses

Our hypotheses are as follows:

Hypothesis 1: Compared to neurotypical controls, autistic adults will display hyper-plasticity (i.e. significantly greater LTP-like plasticity) in the S1.Hypothesis 2: There will be a positive association between plasticity and TR, however, the association will only be significant for the autistic group reflecting hyper-plasticity underlying excessive TR.Hypothesis 3: Autistic adults randomized to active bilateral rTMS will have less LTP-like plasticity in S1 following a single session of active rTMS than those randomized to single session of sham bilateral rTMS.Hypothesis 4: Bilateral active rTMS to S1 will be well-tolerated.

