#### Statistical analysis

Hypothesis 1: To test this hypothesis, we will employ a linear regression model with CEA ratio (LTP-like plasticity) as dependent variable and study groups (autistic and neurotypical controls) as independent variable. Age, sex, hemisphere of PAS-EEG assessment, IQ and pre-PAS CEA (an index of individual baseline cortical excitability) will enter the model as ‘control’ independent variables. To ensure robustness, a model diagnostic will be conducted through visual inspection of model residuals for lack of normality, heteroscedasticity, linearity and outliers [46] and Cook’s distance [47] will be used to inspect for influential data points. Potential confounding effect of medication use among autistic adults on plasticity will be investigated in a post-hoc sensitivity analysis that will include mediation as an additional control.

Hypothesis 2: We will use a multivariate analysis of variance to test this hypothesis where TR, as dependent variable, is associated with plasticity in the autism group; S1 plasticity, study groups and their interaction will be the main predictors; and sex, age, hemisphere of PAS-EEG assessment and IQ will enter the model as controls. If the interaction between S1 plasticity and study group proves to be significant at confidence level 0.05, the model estimated slopes of S1 within each group will be investigate using graphs.

Hypotheses 3 & 4: In order to study the effect of active vs. sham rTMS on LTP-like plasticity, we will use an analysis of covariance with CEA ratio (LTP-like plasticity) as dependent variable, groups (active and sham rTMS) as fixed factor, and pre-rTMS CEA ratio as covariate. We will count discontinuation of rTMS session and adverse events to assess tolerability.

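### The 80% power stated for hypothesis 2 does not apply to a moderate association within the 32 autistic participants, where power is about 53–56%, or about 30–33% for the interaction if controls show no association

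*Protocol article*

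**What the plan says.** The power paragraph (Protocol article, Outcomes) gives a sample "consisting of 32 autistic participants and 32 neurotypical controls". It first justifies this number with 90% power, based on a pilot difference in plasticity. It then says that the same number suits hypothesis 2, "offering an 80% statistical power to detect a moderate effect size", quantified as Cohen's f2 = 0.15. On method it adds only that "These power calculations were executed using G*Power". It does not say which model term the f2 describes.

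The second objective is "To examine the relationship between TR and plasticity in the S1 within both study groups". Hypothesis 2 reads "There will be a positive association between plasticity and TR", with the qualification that "the association will only be significant for the autistic group".

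The Statistical analysis section models tactile reactivity on plasticity, group and their interaction, with sex, age, hemisphere and IQ as controls. The within-group slopes are looked at only if the interaction "proves to be significant at confidence level 0.05".

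**The concern.** The power figure and the hypothesis refer to different quantities. A power of 80% or more at f2 = 0.15 needs a single effect carried by all 64 participants. The association that hypothesis 2 predicts lies in one group of 32. The interaction that must be significant before the slopes are examined is a difference between two slopes, each estimated from 32 people, so it is less precise than either slope alone.

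The Introduction makes the link between S1 hyper-plasticity and atypical tactile reactivity the study's main goal, and hypothesis 2 is the test of that link. A reader told that power is 80% for a moderate effect would take a non-significant interaction as fair evidence against the mechanism. If a moderate association exists only in the autistic group, that reading would be unsafe. The plan emphasises estimates and confidence intervals over significance for the rTMS comparison, but gives no such caution for hypothesis 2.

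**Working it through.** **Inputs.** N = 64, 32 per group, and f2 = 0.15 (Outcomes). Alpha 0.05 (Statistical analysis, given for the interaction). Sidedness is not stated; two-sided is assumed. The model has seven predictors. Hemisphere is constant because only left S1 is assessed, so six can be estimated and 64 − 6 − 1 = 57 residual df remain.

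**1. The plan's own figure.** Power of the regression F test uses the noncentral F distribution with λ = f2 × N = 0.15 × 64 = 9.6.

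| Tested df | Power at N = 64 | N for 80% |
|---|---|---|
| 1 | 86% | 55 |
| 2 | 78% | 68 |
| 3 (plasticity, group, interaction) | 71% | 77 |

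The stated 80% is therefore met for one tested term and missed by about 2 points for two. It is not met for the three main terms jointly.

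**2. What 86% would mean for the interaction.** Put plasticity on a unit-SD scale with residual SD 1. Each slope then has variance of about 1/32, and the difference between slopes 2/32 = 1/16, so λ = 16 × (slope difference)². Setting λ = 9.6 gives (slope difference)² = 9.6/16 = 0.6. If the control slope is zero, this is the within-autism f2, and r = √(0.6/1.6) = 0.61.

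**3. Power if f2 = 0.15 is the within-autism association.** Here r = √(0.15/1.15) = 0.361.

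- F test with n = 32: λ = 0.15 × 32 = 4.8, power 56%.
- Fisher z: atanh(0.361) × √29 − 1.96 = 0.08, power 53%.
- Simulation (20,000 runs, three covariates, control slope zero): 54% for the autism slope in the pooled model and 50% in a separate autism-only regression.

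**4. Power of the interaction in the same scenario.** With a control slope of zero, λ = 16 × 0.15 = 2.4. The F test gives 33%; simulation gives 30%.

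**5. Effects needed for 80%.**

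- Autism slope: f2 about 0.26 by the F formula, r = √(0.26/1.26) = 0.45; about 0.29 by simulation in the pooled model, r = √(0.29/1.29) = 0.47.
- Interaction, control slope zero: the F test with 1 and 57 df needs λ of about 8.1, so within-autism f2 is about 8.1/16 = 0.51 (r about 0.58). In simulation f2 = 0.60 (r about 0.61) gives 81%. Both round to r of about 0.6.
- At f2 = 0.15, 80% power for the slope would need about 55 autistic participants.

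**The case against.** The strongest defence is that the planned decisive test is the interaction, with one degree of freedom in all 64 participants. In regression power software the f2 of a tested term is that term's own partial effect. On that reading power is 86% and 80% is a conservative statement. The article also never says that 64 was solved for hypothesis 2; the number is introduced with the group comparison and then called suitable for this one. A mismatch with 55, 68 or 77 is therefore no error.

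This stands, and it rules out a stronger reading that a reader might draw from the table: that the 80% is an arithmetic mistake which no standard calculation reproduces. The one-term test exceeds 80% and the two-term test comes within about 2 points. A two-sided alpha of 0.025 gives 78.6%, and a noncentrality based on degrees of freedom with one tested term gives 81–82%.

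It is also fair that 30–33% is not the power of the trial without conditions. It assumes that f2 = 0.15 describes the autism slope and that the control slope is zero. The article states neither; it predicts only that the association will not be significant in controls. Finally, an article may leave the tested term and its df to a fuller document, so their absence alone is no fault.

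What the defence does not remove is the conflict with the word moderate. To keep f2 = 0.15 for the interaction with no association in controls, the within-autism correlation must be about 0.61.

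**Conclusion.** The point holds as a mismatch between the stated power and the hypothesis it is said to serve. The 80% is defensible for a single term with partial f2 = 0.15 in all 64 participants. It does not hold for a moderate association within the autistic group: power there is about 53–56% (50% in the least favourable calculation), so such an association would be missed nearly half the time. If in addition the control slope is zero, the interaction test would miss it about 70% of the time.

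These figures assume two-sided alpha 0.05, equal residual variance, equal spread of plasticity in the two groups, and complete data on 32 per group. The documents do not support calling the 80% a computational error, nor quoting 30–33% without its condition.

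**What to change.** In the power paragraph, name the tested term, its degrees of freedom and the alpha to which f2 = 0.15 applies, and replace the single 80% for hypothesis 2 with wording such as:

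> With 32 autistic participants, power is about 53–56% for a within-autism association of f2 = 0.15, and 80% for a correlation of about 0.45–0.47. Assuming no association in controls, the plasticity by group interaction has about 30% power at f2 = 0.15 within autism and reaches 80% only at a within-autism correlation of about 0.6.

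If the authors did mean the interaction's own partial effect, they should say so, give the 86%, and state the within-autism correlation it implies. Design, sample size and analysis are unchanged. The cost is a less favourable stated power for the hypothesis that carries the study's main goal.

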#### Statistical analysis

Hypothesis 1: To test this hypothesis, we will employ a linear regression model with CEA ratio (LTP-like plasticity) as dependent variable and study groups (autistic and neurotypical controls) as independent variable. Age, sex, hemisphere of PAS-EEG assessment, IQ and pre-PAS CEA (an index of individual baseline cortical excitability) will enter the model as ‘control’ independent variables. To ensure robustness, a model diagnostic will be conducted through visual inspection of model residuals for lack of normality, heteroscedasticity, linearity and outliers [46] and Cook’s distance [47] will be used to inspect for influential data points. Potential confounding effect of medication use among autistic adults on plasticity will be investigated in a post-hoc sensitivity analysis that will include mediation as an additional control.

Hypothesis 2: We will use a multivariate analysis of variance to test this hypothesis where TR, as dependent variable, is associated with plasticity in the autism group; S1 plasticity, study groups and their interaction will be the main predictors; and sex, age, hemisphere of PAS-EEG assessment and IQ will enter the model as controls. If the interaction between S1 plasticity and study group proves to be significant at confidence level 0.05, the model estimated slopes of S1 within each group will be investigate using graphs.

Hypotheses 3 & 4: In order to study the effect of active vs. sham rTMS on LTP-like plasticity, we will use an analysis of covariance with CEA ratio (LTP-like plasticity) as dependent variable, groups (active and sham rTMS) as fixed factor, and pre-rTMS CEA ratio as covariate. We will count discontinuation of rTMS session and adverse events to assess tolerability.

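### Hypothesis 2 concerns the plasticity–TR association within groups, but the plan examines the within-group slopes only after a significant interaction, and then by graphs with no stated test or interval

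*Protocol article*

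**What the plan says.** The second objective (Objectives) is "To examine the relationship between TR and plasticity in the S1 within both study groups". The matching hypothesis (Hypotheses) begins "There will be a positive association between plasticity and TR" and adds that significance is expected in the autistic group only.

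For the analysis, the Hypothesis 2 paragraph of the Statistical analysis section says: "We will use a multivariate analysis of variance to test this hypothesis where TR, as dependent variable". The main predictors are S1 plasticity, study group and their interaction. Sex, age, hemisphere and IQ are controls. The follow-up rule is: "If the interaction between S1 plasticity and study group proves to be significant at confidence level 0.05", then "the model estimated slopes of S1 within each group will be investigate using graphs". Nothing is said about what happens when the interaction is not significant.

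The power paragraph under Outcomes gives a total of 64, "consisting of 32 autistic participants and 32 neurotypical controls". For Hypothesis 2 it describes this number as "offering an 80% statistical power to detect a moderate effect size", with Cohen's f2 = 0.15. It does not say which model term that f2 belongs to.

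**The concern.** Three questions are involved. Is there an association in autistic adults? Is there one in controls? Do the two differ? The objective and the hypothesis are worded around the first two. The only significance test that the paragraph specifies answers the third, and it decides whether the first two are looked at.

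Even when the interaction is significant, a graph cannot show that an association is significant in one group and not in the other. When it is not significant, the stated procedure ends without a result for either group.

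This matters because the Introduction describes whether S1 hyper-plasticity underlies atypical TR as the study's primary goal, and the Hypothesis 2 model is the only planned analysis that links plasticity to TR.

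**Working it through.** **Inputs from the article.** 32 autistic and 32 control participants; significance level 0.05 for the interaction; three main predictors; four named controls. Only left S1 is assessed, so hemisphere does not vary and three controls can be estimated. With the intercept the model has 7 parameters, leaving 64 − 7 = 57 residual degrees of freedom.

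**Assumptions, not in the article.** Two-sided testing, no dropout, the same residual SD and the same plasticity SD in both groups, and the within-group correlations below.

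**Step 1: the plan's own power figure.** For a regression F test, the noncentrality is f2 × N = 0.15 × 64 = 9.6.

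| Predictors tested | Power at N = 64 | N for 80% |
|---|---|---|
| 1 | 86.1% | 55 |
| 2 | 77.5–77.7% | 68 |
| 3 | 71% | 77 |
| all 7 | 53% | – |

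No choice returns 80% exactly. One tested predictor meets it as a minimum; two come closest, just short. The figure therefore does not reveal which term was meant.

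**Step 2: approximate power of the two tests.** With residual SD 1 and plasticity SD 1, a correlation r corresponds to a slope b = r/√(1 − r²).
- Autistic slope: noncentrality b × √32.
- Interaction: noncentrality (difference in slopes) × √(32/2) = difference × 4.

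If f2 = 0.15 describes the autistic slope alone and the control slope is 0, then r = √(0.15/1.15) = 0.361 and b = √0.15 = 0.387.
- Autistic slope: 0.387 × √32 = 2.19, power 57.6%.
- Interaction: 0.387 × 4 = 1.55, power 33.1%.

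If f2 = 0.15 is instead the interaction's own effect, the slope difference is 2 × √0.15 = 0.775, which is r of about 0.61 in autistic adults with a control slope of 0. The noncentrality is 0.775 × 4 = 3.10 and the power 86.1%.

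The interaction reaches 50% power at a slope difference of about 0.50 (autistic r about 0.45, control 0).

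**Step 3: simulation of the full model with three covariates.** These values are slightly lower than in step 2, because plasticity and the covariates vary from sample to sample.

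| Correlation, autistic / control | Interaction significant | Autistic slope significant |
|---|---|---|
| 0.36 / 0 | 30% | 53% |
| 0.5 / 0 | 57% | 85% |
| 0.6 / 0 | 79% | 97% |
| 0.5 / 0.2 | 29% | 84% |

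Repeat runs agree to within one or two points (77–79% and 96–97% in the third row; 28–29% and 84–85% in the fourth).

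**Step 4: equal slopes.** With correlation 0.36 in both groups, the interaction is significant in 5% of trials. The plasticity effect averaged over groups, from the same model, is significant in about 80%. This case is not Hypothesis 2, but Objective 2 would still need both slopes reported.

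**The case against.** The other side has substantial points.

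- **The interaction is the right test of a difference between groups.** A significant slope in one group and a non-significant one in the other does not show that the slopes differ. Examining slopes after a significant interaction is conventional. This stands: the interaction should be kept. It does not justify withholding the slopes when the interaction is not significant.
- **The article is condensed.** Slope tables and intervals may be in a fuller plan. However, the point is a conditional rule that the article does state; a plan that reported the slopes unconditionally would depart from it.
- **A direct test is no full rescue.** With 32 autistic participants, power for a moderate slope (r = 0.36) is only about 53%. True, and a further reason to report intervals.

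A reader might also infer four stronger things, which the documents do not support:

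- *That the question goes unanswered in most trials in which the hypothesis is true.* This depends on effect sizes that are not given. It holds at 0.36/0 and 0.5/0.2. It fails at 0.5/0 and 0.6/0, and if f2 = 0.15 is the interaction effect.
- *That equal slopes would lead to a report of no association at all.* Plasticity is itself a main predictor, and its average effect would be significant in about 80% of trials (step 4).
- *That the method gives no slope estimate.* The text refers to slopes estimated by the model, and the listed predictors yield both. What is missing is a commitment to test them or give intervals.
- *That the rule has its own large exaggeration effect.* At 0.36/0 the autistic slope is overestimated by about 40% when selected through the interaction, but by about 35% when selected on its own p-value. This is ordinary selection on significance at low power.

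**Conclusion.** The point holds in a limited form. The stated rule does not directly test Hypothesis 2 as worded, and it makes the answer to Objective 2 depend on a different question. That conclusion comes from the text alone and needs no assumed effect size.

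The loss does depend on assumptions. In the four scenarios of step 3, the chance of reaching the slopes is between 18 and 55 percentage points lower than the chance that a direct autistic-slope test is significant (97 − 79 = 18 at 0.6/0; 84 − 29 = 55 at 0.5/0.2). If f2 = 0.15 belongs to the interaction itself, the slopes are reached in about 86% of trials. All these figures rest on two-sided testing, complete data, and equal residual and plasticity SDs in the two groups.

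The method's name is a smaller matter: with one dependent variable, multivariate analysis of variance is a misnomer for what is a linear regression.

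**What to change.** Rewrite the Hypothesis 2 paragraph before the data are analysed, since slope tests added after seeing the interaction would be post hoc:

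1. Fit one linear regression of TR on plasticity, group, their interaction and the covariates, and call it that.
2. Report the autistic slope with its test, the control slope, and the difference between them, each with a 95% CI, whatever the interaction p-value.
3. Keep the interaction as the test of group specificity and the graphs as illustration.
4. In the power paragraph, state which term f2 = 0.15 refers to and how many predictors are tested.

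The cost is wording only. No data, participants or procedures change, because the planned model already yields both slopes.

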Our primary goal is to test whether the S1 hyper-plasticity underlies atypical TR in autism. In this study, we will use the innovative combination of paired associative stimulation (PAS), a well-established TMS paradigm to study plasticity, and electroencephalography (EEG) or PAS-EEG, to assess plasticity [21]. In PAS-EEG experiment, PAS induced LTP-like (i.e. PAS-LTP-like) is defined by potentiation of cortical evoked activity (CEA), which is measured by EEG. The reproducibility of the PAS-EEG method was reported in independent samples [22,23]. We will also explore if a single session of ‘mechanism-driven’ rTMS [15] described above can reduce hyper-plasticity in the S1 and whether it is well-tolerated by autistic adults.

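### Hypothesis 2 concerns the plasticity–TR association in autistic adults, but the within-group slopes are examined only after a significant interaction, and then only on graphs

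*Protocol article*

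**What the plan says.** The Introduction states the aim: "Our primary goal is to test whether the S1 hyper-plasticity underlies atypical TR in autism". Objective 2 reads: "To examine the relationship between TR and plasticity in the S1 within both study groups, i.e. autistic and neurotypical". The Hypotheses section predicts: "There will be a positive association between plasticity and TR, however, the association will only be significant for the autistic group". The target is thus a slope within a group, with the autistic group first in importance.

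Under Hypothesis 2, the Statistical analysis section names this method: "We will use a multivariate analysis of variance to test this hypothesis where TR, as dependent variable, is associated with plasticity in the autism group". The main predictors are plasticity, group and their interaction; sex, age, hemisphere and IQ are controls. The Outcomes section gives one TR measure, the SPQ touch score.

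The next step is conditional: "If the interaction between S1 plasticity and study group proves to be significant at confidence level 0.05", then "the model estimated slopes of S1 within each group will be investigate using graphs". No step is given for a non-significant interaction. The power section gives Hypothesis 2 80% power at N = 64 for f² = 0.15 and does not say which term that effect belongs to. The article's commitment to 95% confidence intervals stands in the paragraph on the rTMS comparison, not under Hypothesis 2.

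**The concern.** The plan's decision rule and its hypothesis address different quantities. The interaction asks whether the two slopes differ. Hypothesis 2 asks first whether the autistic slope is positive. If plasticity and TR are related in both groups, or more strongly in one but not by enough to detect, the interaction will usually be non-significant and the plan gives no reason to look at the autistic slope. If the interaction is significant, the slopes are drawn but no interval or test is attached to them.

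The plasticity term does not fill the gap. In a model with an interaction, its coefficient depends on how group is coded: it is the control slope, the autistic slope, or an average of the two. The plan states neither the coding nor how this term will be read.

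The wording of Hypothesis 2 adds a second risk. It treats significance in one group and non-significance in the other as the expected pattern. A non-significant slope in 32 controls is weak evidence that no association exists there.

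**Working it through.** **Inputs.** N = 64, 32 per group, and f² = 0.15 with 80% power (power section). Significance level 0.05 (Statistical analysis). Two-sided testing is my assumption, because sidedness is not stated. There are three main predictors and four controls. Hemisphere is constant, since only left S1 is assessed, so six predictors remain.

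**Step 1: the plan's own figure.** I used the noncentral F test for added terms in a multiple regression, with noncentrality λ = f² × N = 0.15 × 64 = 9.6 and residual df = 64 − 6 − 1 = 57.

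| Terms tested together | Power at N = 64 |
|---|---|
| 1 | 86% |
| 2 | 78% |
| 3 | 71% |

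No choice gives exactly 80%. Read as at least 80%, the figure is met for any single term, including the interaction, provided f² = 0.15 is that term's own partial effect.

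**Step 2: if f² = 0.15 describes the association in autistic adults.** Assume a zero control slope, equal residual variance and equal plasticity variance in the groups. An f² of 0.15 within a group corresponds to r = √(0.15/1.15) = 0.36. With equal groups, the interaction column has one quarter of the plasticity variance left after adjustment for group and plasticity. So:

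- interaction f² = 0.15 / 4 = 0.0375, λ = 0.0375 × 64 = 2.4, power about 33%;
- autistic slope in the same model: λ = 0.15 × 32 = 4.8, power about 58%.

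These formulas hold the predictors fixed. Simulating them as random (20,000 trials, pooled model, three other controls) gives slightly lower values.

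| Scenario | Interaction significant | Autistic slope significant | Autistic slope significant, interaction not |
|---|---|---|---|
| Autistic f² = 0.15, control slope 0 | 30% | 53% | 26% |
| Same slope in both groups (f² = 0.15 each) | 5% | 53% | about 51% |

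If residual variance is instead set so that total TR variance is equal in the groups, the first row becomes 29%, 50% and 26%.

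**Step 3: what 86% for the interaction would require.** Reversing step 2, an interaction f² of 0.15 with a zero control slope needs an autistic f² of 4 × 0.15 = 0.60, or r = √(0.60/1.60) = 0.61. That is well above what the article calls a moderate effect, if the word is meant for the within-group association.

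**Step 4: the control slope.** By symmetry with the 53% above, a control slope with f² = 0.15 would be non-significant in about 100 − 53 = 47% of trials. Non-significance in controls therefore cannot be read as absence.

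**The case against.** The strongest replies are these.

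- *The slopes are estimated.* This stands. The text speaks of slopes estimated by the model, so a reader who infers that the association is never estimated goes too far. What is missing is a stated test or interval, and any use of the slopes when the interaction is non-significant.
- *The interaction is not the only term.* This stands too. Plasticity is listed as a main predictor, so it would be wrong to say that the plan tests the interaction alone. But that term does not by itself give the autistic slope, so it does not answer Hypothesis 2.
- *The interaction is not shown to be underpowered.* A reader might infer from the 30% that it is. The documents do not support that as a fact: if f² = 0.15 is the interaction's partial effect, power is 86%. The supportable point is that the term is unnamed and the answer depends heavily on it.
- *Testing the interaction before comparing slopes is conventional.* It does protect claims of a group difference, and the interaction should remain the only basis for such a claim. It does not serve a hypothesis about one group's slope.
- *The method label is harmless.* Largely true. With one dependent variable, a multivariate analysis of variance reduces to the ordinary linear model, and no result changes.
- *An unseen analysis plan may tabulate intervals.* It may. But the article itself fixes the condition and the graphical follow-up, and those are what need changing.

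**Conclusion.** The point holds in this form: the stated procedure can leave the association that Hypothesis 2 is about, which the article presents as its main aim, without a test or interval. This follows from the text and needs no assumption about effect size.

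How often it would matter is conditional. With f² = 0.15 as the autistic association and no slope in controls, about one trial in four would have a significant autistic slope that the plan does not examine. With equal slopes in both groups it would be about one in two. These figures assume two-sided 0.05 tests, equal plasticity variance and independent normal errors. Under the same reading, a direct test of the autistic slope has only about 53% power, so the change improves the analysis but does not reach 80%.

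**What to change.** Replace the Hypothesis 2 paragraph with wording such as:

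*TR (SPQ touch score) will be analysed by linear regression on plasticity, group, plasticity × group, age, sex and IQ. The plasticity slope in the autistic group, with its test and 95% CI, is the result for Hypothesis 2. The control slope and the difference between slopes will be reported with 95% CIs whatever the interaction p-value. A difference between groups will be claimed only from the interaction.*

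Hemisphere drops out because only left S1 is assessed. Replacing the multivariate label is a wording correction. Hypothesis 2 should no longer rest on a non-significant control slope. The power section should name the term to which f² = 0.15 applies and restate the figure if that term is the autistic slope.

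The cost is text only: same data, same informative predictors, no extra participants. The downsides are one more reported test and possibly a less favourable power figure.
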